### Sample Size

The sample size involved estimation of the number of clusters (IRIS) using a composite outcome, “well-managed” women, which is defined as those women who completed a valid HPVss test and were either advised of a negative result (in the case of HPVss-negative women) or completed the assessment (in the case of HPVss-positive women), and, where necessary, treatment pathway. The following assumptions were considered:

Expected average cluster size of 250 eligible women; this is an estimate of the number of women in the target age range (30-65 years) within a cluster of 2000 people, based on the population pyramid of ages in the Occitanie Region.Expected proportion of overall well-managed women in the control group of 15%.Expected absolute increase of 10% in the proportion of overall well-managed women in the experimental group.Coefficient of variation taking into account the possibility of varying cluster sizes of 1.2 (arrived at because of the wide level of dispersion around the mean cluster size) [26].A 10% precision in the proportion of overall well-managed women, which would lead to a 0.029 intracluster correlation using a beta-binomial model [27].A power of 80% and a 5% 2-tailed significance level.

Under the aforementioned assumptions, the required number of clusters to randomize in each arm would be 10 (total: 20 clusters). However, if subgroup analyses are to be performed, stratifying on general population density, medical density of the department (high or low), and setting of the community (rural or urban), taking into consideration these α adjustments (α=.3125% [2.5%/8]) for each of the subgroup analyses in order to be able to remain with a 5% 2-tailed significance level for the overall effect, approximately 16 clusters in each arm (32 clusters in total) will be required for the subgroup analyses.

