**Methods:**

AppDate-You is a 2-arm cluster randomized controlled trial (cRCT) nested within the French organized CCS program. Eligible women are those aged 30-65 years who have not been screened for CC for more than 4 years and live in the disadvantaged clusters in the Occitanie Region, France. In total, 32 clusters will be allocated to the intervention and control arms, 16 in each arm (approximately 4000 women). Eligible women living in randomly selected disadvantaged clusters will be identified using the Regional Cancer Screening Coordinating Centre of Occitanie (CRCDC-OC) database. Women in the experimental group will receive screening reminder letters and HPVss kits, combined with access to a chatbot-based decision aid tailored to women with lower education attainment. Women in the control group will receive the reminder letters and HPVss kits (standard of care). The CRCDC-OC database will be used to check trial progress and assess the intervention’s impact. The trial has 2 primary outcomes: (1) the proportion of screening participation within 12 months among women recalled for CCS and (2) the proportion of HPVss-positive women who are “well-managed” as stipulated in the French guidelines.

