## Introduction

### Background

In France, there were an estimated 2920 new cervical cancer (CC) cases and 1117 related deaths in 2018, with marked geographical disparities within regions [1]. A decline in CC incidence and mortality rates was observed during the period of 1990 to 2018, although this was less pronounced in recent years [1]. The prognosis of CC is deteriorating in France, with a 5-year survival rate after diagnosis decreasing from 68% in 1989 to 1993 to 62% in 2005 to 2010 [2]. During the period of 2018 to 2020, the national triennial coverage rate was 59.2%, with a strong geographical disparity within French departments, ranging from 11.8% to 65% [3]. The national screening coverage rate appeared relatively stable since 2012 across the age groups and declined markedly in women older than 50 years, down to 44.2% in women aged 60 to 65 years [4].

The French organized population-based CC screening (CCS) program shifted from a cytology-based to a human papillomavirus (HPV)–based screening strategy in August 2020. HPV testing is offered every 5 years, starting at the age of 30 years. In the new program, women are invited to have the HPV test at a gynecologist’s, primary care physician’s, or midwife’s office, a private clinic or health center, family planning center, or hospital. A reminder letter is sent to noncompliant women after 12 months from the date of the first screening invitation.

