### Study Population

Eligible women are those aged 30-65 years who did not respond to an initial invitation letter to have an HPV test collected by a clinician, have not been screened for CC for more than 4 years, and live in the disadvantaged clusters in the Occitanie Region.

Women will be excluded from the study if they have undergone CC screening within the past 4 years, have had a hysterectomy, or have been diagnosed with and are receiving treatment for precancer or CC.

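### The cluster size of 250 behind the 10 and 16 clusters per arm counts women in the age range, not women eligible under the protocol's own rule, and the total number of women is ambiguous

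*Protocol article*

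**What the plan says.** The Sample Size section of the protocol article lists its inputs:

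- "Expected average cluster size of 250 eligible women", explained as follows: "this is an estimate of the number of women in the target age range (30-65 years) within a cluster of 2000 people"
- 15% well-managed women in the control arm and an absolute increase of 10 points
- "Coefficient of variation taking into account the possibility of varying cluster sizes of 1.2"
- an intracluster correlation of 0.029
- 80% power at a two-sided 5% level.

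From these it concludes that "the required number of clusters to randomize in each arm would be 10 (total: 20 clusters"). With alpha set at 2.5%/8 = 0.3125% for the subgroup analyses, it arrives at about 16 per arm, which is the number to be randomized.

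Study Population sets a narrower rule. Besides being aged 30-65, women must not have responded to the first invitation and must "have not been screened for CC for more than 4 years, and live in the disadvantaged clusters in the Occitanie Region". Hysterectomy and current treatment for precancer or cancer are exclusions.

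The abstract says that "32 clusters will be allocated to the intervention and control arms, 16 in each arm (approximately 4000 women"). The Statistical Analysis section says only that logistic regression will adjust for the cluster design. It does not say how clusters of different size are weighted.

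**The concern.** The label and the definition of the 250 do not agree. A count based on age and the population pyramid is not a count of women who also ignored an invitation and have gone unscreened for more than 4 years. The eligible women are a subset, so if the definition is taken at its word, the mean cluster size is overstated.

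The abstract does not settle the matter, because its total fits 250 per cluster on one reading and half of that on the other.

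Three things depend on this number: the clusters needed for the overall effect, the clusters needed at the adjusted alpha, and the number of HPV-positive women. The last of these is the denominator of the second primary outcome. The formula that used the 1.2 is not shown either, and the answer is sensitive to it.

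**Working it through.** **Inputs (Sample Size section).** Proportions 0.15 and 0.25; m = 250; ICC = 0.029; CV = 1.2; 80% power; 5% two-sided; adjusted alpha 0.3125%, read here as per tail because it is 2.5%/8.

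**1. Women per arm without clustering.** The variance sum is 0.1275 + 0.1875 = 0.315.
- At 5%: (1.960 + 0.8416)² × 0.315 / 0.10² = 247.2.
- At 0.3125% per tail: (2.734 + 0.8416)² × 0.315 / 0.10² = 402.8.

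**2. Equal clusters.** Design effect (DE) = 1 + 249 × 0.029 = 8.221. Clusters per arm = 247.2 × 8.221 / 250 = 8.13.

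**3. Reproducing the plan's 10 and 16.** For an efficiently weighted analysis (mixed model or exchangeable correlation), the relative efficiency is RE = 1 − CV² × L(1 − L), with L = m·ICC / (m·ICC + 1 − ICC).
- L = 7.25 / 8.221 = 0.882, so RE = 1 − 1.44 × 0.882 × 0.118 = 0.850.
- DE = 8.221 / 0.850 = 9.67.
- Overall: 247.2 × 9.67 / 250 = 9.56, so 10.
- Adjusted alpha: 402.8 × 9.67 / 250 = 15.6, so 16.

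Ten per arm then give 82% power by the normal approximation and 77% by t with 18 df, so a t-based count is 11. Using 1.2 as a plain multiplier also gives the stated figures: 8.13 × 1.2 = 9.76 and 13.25 × 1.2 = 15.9. In that case, however, 1.2 is not a coefficient of variation.

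**4. Totals.** 16 × 250 = 4000 and 32 × 250 = 8000. If 4000 is the overall total, 4000 / 32 = 125 per cluster.

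**5. Same method, smaller clusters.** The documents give no count of eligible women per cluster, so the sizes below are assumptions. 125 is the second reading of the abstract. About 100 comes from the Background, where "the national triennial coverage rate was 59.2" percent: 250 × 0.408 = 102. 60 is a low bound. Power = Φ(0.10 / √(0.315 × DE / (k·m)) − z). For example, m = 125 and k = 16 give 3.240 − 1.960 = 1.280, so 90%.

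| m | RE | DE | Clusters per arm, overall | Clusters per arm, 0.3125% per tail | Power of 10 (z / t) | Power of 16 (z / t) | Power of 16 at 0.3125% per tail (z) |
|---|---|---|---|---|---|---|---|
| 250 | 0.850 | 9.67 | 9.6 | 15.6 | 82% / 77% | 95% / 94% | 81% |
| 125 | 0.760 | 6.05 | 12.0 | 19.5 | 73% / 68% | 90% / 88% | 69% |
| 100 | 0.729 | 5.31 | 13.1 | 21.4 | 69% / 64% | 87% / 85% | 64% |
| 60 | 0.669 | 4.05 | 16.7 | 27.2 | 58% / 54% | 78% / 76% | 50% |

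The adjusted-alpha columns use all clusters of an arm, since that is what reproduces the plan's 16.

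**6. If clusters are weighted by size.** DE = 1 + ((1 + 1.44) × 250 − 1) × 0.029 = 18.66, and 247.2 × 18.66 / 250 = 18.5 clusters per arm. The planned 16 then give 74% (z) or 71% (t), even at m = 250.

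**The case against.** The strongest defence is that the calculation is coherent. One recognised method, with the CV of 1.2 included, returns both 10 and 16. A reader might infer from the size-weighted formula that 10 does not follow from the inputs and should be replaced by 19. The documents do not support that. The size-weighted formula is correct for a size-weighted analysis, but the Statistical Analysis section does not commit to one, and a mixed or exchangeable model would not weight that way. This defence stands. A condensed article may also leave the formula to a fuller document, so its absence alone would not be a finding.

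It is also fair to say that the trial randomizes 16 per arm, not 10, and that the ICC dominates, so smaller clusters cost only moderate power. Both points stand for the overall effect. Likewise, the abstract's 4000 is ambiguous and not shown to be wrong, because read per arm it equals 16 × 250.

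The figure of about 100 eligible women is soft. It applies a national three-year coverage rate to selected deprived areas and to a different, four-year criterion. The Background also says that women in disadvantaged areas take part less, so eligibility there may be higher than that rate suggests. It is also possible that the 250, which is 12.5% of 2000 residents, has already been reduced to unscreened women. The text does not say so; it describes a count by age.

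None of this removes the conflict between the definition of the 250 and the eligibility rule.

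**Conclusion.** The point holds as an inconsistent input. The 250 is labelled as eligible women but defined by age alone, which contradicts Study Population, and the abstract's total leaves open whether the mean is 250 or 125.

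The stated 10 and 16 hold only if three conditions are met: there really are 250 eligible women per cluster; the analysis weights clusters efficiently (or 1.2 was a plain multiplier); and a normal approximation is accepted.

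Under the efficient-weighting method, with 100 to 125 eligible women per cluster:

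- the overall effect needs 12.0 to 13.1 clusters per arm, and 10 give 69 to 73% power by z or 64 to 68% by t;
- the adjusted alpha needs 19.5 to 21.4, so 16 no longer suffice there;
- the planned 16 still give about 85 to 90% for the overall effect.

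A reader might conclude that the trial is underpowered for its overall effect. That follows only if the analysis is size-weighted (71 to 74% at m = 250) or if eligible women per cluster are far fewer than 100. The documents establish neither.

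**What to change.** - Take the number of eligible women in each selected IRIS from the CRCDC-OC database, which the Randomization section already names as the source for identifying them. Recompute with the observed mean and CV.
- Restate the clusters required, and the power that 16 per arm deliver for the overall effect and at the adjusted alpha.
- State that the analysis will use an efficiently weighted model (mixed or exchangeable), so that it matches the calculation.
- Say whether 1.2 is a coefficient of variation or an inflation factor. If it is the latter, give the CV.
- Give one total of women, labelled per arm or overall, in the abstract and the Sample Size section.

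The cost is a database count, a recalculation and some restated figures. With efficient weighting and about 100 or more eligible women per cluster, no clusters need be added for the overall effect. The downside is that the stated power, above all at the adjusted alpha, may become less favourable.

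### The 2.5%/8 subgroup adjustment is said to keep 5% two-tailed for the overall effect, but it cannot: the stated levels add to 7.5%, or 10% if 0.3125% is per tail

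*Protocol article*

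**What the plan says.** All of this stands in the protocol article, Methods, Sample Size.

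- The overall comparison is sized with "A power of 80% and a 5% 2-tailed significance level", giving 10 clusters per arm (20 in total).
- Subgroup analyses are introduced conditionally ("if subgroup analyses are to be performed"), on three factors: "stratifying on general population density, medical density of the department (high or low), and setting of the community (rural or urban".
- They are sized by "taking into consideration these α adjustments (α=.3125% [2.5%/8]) for each of the subgroup analyses", and the stated purpose is "in order to be able to remain with a 5% 2-tailed significance level for the overall effect". This raises the requirement to about 16 clusters per arm (32 in total), and the Abstract adopts 32.

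The section does not say whether 0.3125% is two-sided or per tail, does not give the levels of general population density, and does not assign the overall test any level other than 5%. The Statistical Analysis section does not mention subgroup tests or multiplicity.

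**The concern.** The plan states a rule for alpha and a reason for it, and the two do not fit. A test carried out at 5% has a 5% error rate whatever level is used for other tests. A smaller subgroup alpha limits what the subgroups add to the total; it does not protect the overall test. If the overall test already uses the full 5%, any further test that can lead to a claim by itself takes the total above 5%.

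The subgroup analyses are not a side issue in this design, since they account for the move from 20 to 32 clusters (32/20 = 1.6, or 60% more). The Discussion expects a successful result to inform policy makers and local guidelines. A claim that the chatbot works in one type of area, made after a null overall result, would appear to be covered by a 5% safeguard that the stated levels do not provide.

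**Working it through.** **Inputs (Sample Size section).** Overall test 5% two-tailed, power 80%; subgroup alpha 0.3125%; control proportion 15%; increase of 10 points, so 25%; mean cluster size 250; intracluster correlation 0.029; coefficient of variation 1.2.

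**1. The plan's own figure.** 2.5%/8 = 0.3125%, exact. Three factors at two levels each give 2 × 2 × 2 = 8 cells, which matches the divisor. Two levels for population density is an assumption.

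**2. Sum of the stated levels.**
- 0.3125% two-sided: 5% + 8 × 0.3125% = 7.5%.
- 0.3125% per tail (0.625% two-sided): 5% + 8 × 0.625% = 10%.
- If the overall test had 2.5% and 0.3125% were two-sided: 2.5% + 8 × 0.3125% = 5%.

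**3. Chance of at least one false claim.** One outcome, no true effect anywhere, and a claim possible from any test. For eight equal disjoint cells the subgroup statistics Z1 to Z8 are independent standard normal and the overall statistic is their sum divided by √8, so each correlates 1/√8 = 0.35 with the overall test. Simulation with 4 million draws:

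| Subgroup layout | Overall 5%, each 0.3125% two-sided | Overall 5%, each 0.625% two-sided | Overall 2.5%, each 0.3125% two-sided | Overall 2.5%, each 0.625% two-sided |
|---|---|---|---|---|
| Eight equal disjoint cells | 7.0% | 9.0% | 4.7% | 6.9% |
| Eight unequal disjoint cells (weights 0.05 to 0.4) | 7.0% | 9.0% | 4.6% | 6.8% |
| Six one-factor subgroups | 5.6% | 6.5% | 3.4% | 4.5% |
| Eight overlapping one-factor subgroups | 5.8% | 6.9% | 3.7% | 5.1% |

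As a check, treating all nine tests as independent gives 1 − 0.95 × (1 − 0.003125)^8 = 7.3% and 1 − 0.95 × (1 − 0.00625)^8 = 9.6%, just above the disjoint-cell results, as expected.

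With the overall test at 5%, every layout exceeds 5%. With eight disjoint cells, only the 2.5% overall test with 0.3125% two-sided stays within it.

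**4. Do the cluster numbers settle which reading was meant?** Women per arm before clustering, for 15% against 25% at 80% power (pooled formula): 250 at 5%, 303 at 2.5%, 408 at 0.625% and 460 at 0.3125%, all two-sided. Design effect without cluster-size variation: 1 + 249 × 0.029 = 8.221. Clusters per arm = n × 8.221/250:

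| Variant | 5% | 2.5% | 0.625% two-sided | 0.3125% two-sided |
|---|---|---|---|---|
| No coefficient of variation | 8.22 | 9.96 | 13.42 | 15.13 |
| Multiplied by 1.2 | 9.87 | 11.96 | 16.10 | 18.15 |
| One cluster added | 9.22 | 10.96 | 14.42 | 16.13 |

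Two variants with the overall test at 5% give 10 and about 16. The plain multiplier does so with 0.3125% per tail, and one added cluster does so with 0.3125% two-sided. The usual variable-cluster-size design effect, 1 + ((1.2² + 1) × 250 − 1) × 0.029 = 18.66, gives 19 clusters at 5% and reproduces neither number. The sample size therefore does not settle the sidedness.

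**The case against.** **The clause may refer to the overall test alone.** It names the overall effect and does not clearly promise 5% across overall and subgroup tests together. A reader might infer that the plan promises a family-wise 5% and breaks it; the wording does not support that. On the narrower reading nothing is contradicted, but the reason given for the adjustment is still wrong, because the overall test stays at 5% with or without it.

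**The 5% may describe another allocation.** Taken per tail, eight tests at 0.3125% use 8 × 0.625% = 5% two-sided, so the 5% might describe the subgroup family. Alternatively, 2.5%/8 may be half of a 2.5% + 2.5% split, which does stay within 5%. Ignoring the coefficient of variation and rounding up even gives 10 clusters at 2.5% and 16 at 0.3125% two-sided. However, that variant sets aside both the stated coefficient of variation and the stated 5%, at which it gives 9. In the two variants that give 10 at 5%, an overall test at 2.5% needs 11 or 12. Nowhere does the text give the overall test 2.5%.

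**The size of the excess depends on the layout.** This stands. A reader might take 7% to 9% as the trial's error rate, but it needs eight disjoint cells, and the section does not say whether the factors are crossed. A reader might also infer that 16 clusters imply the per-tail reading, with the subgroups spending a second full 5%; the second table above shows otherwise.

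**Order and status of the tests may be set elsewhere.** Subgroup testing is conditional, and an analysis plan not shown may add a gate or an exploratory label. So the absence of a gate in the article is not the error, and that the subgroups are confirmatory is an inference from their assigned alpha and their effect on trial size. A later document would still leave the printed reason incorrect.

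**Conclusion.** The point holds in a limited form. The Sample Size section gives its subgroup alpha a purpose that the adjustment does not achieve. As stated, the levels add to 7.5%, or 10% if 0.3125% is per tail. If the overall and subgroup tests can each support a claim, the chance of a false one for a single outcome is about 7.0% or 9.0% with eight disjoint cells, and about 5.6% to 6.9% with one-factor or overlapping subgroups. These figures assume no true effect anywhere and no gate between the tests. The excess over 5% is moderate. The documents do not show a broken family-wise guarantee, nor do they fix the sidedness of 0.3125%.

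**What to change.** In the Sample Size section:

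1. State whether 0.3125% is two-sided, and whether the 5% covers the overall test, the subgroup family or both. If the overall test was meant to be at 2.5%, say so.
2. Replace the clause saying that the subgroup adjustment preserves 5% for the overall effect.
3. Choose one of two rules:
   - **Gate.** Subgroups are tested confirmatorily only if the overall test is significant at 5% two-sided, and the eight subgroup tests together use no more than that 5%: at most 5%/8 = 0.625% two-sided each. The stated 0.3125% satisfies this on either reading. If there is no overall effect, any claim first needs a false-positive overall test, so the error is at most 5%. If there is an overall effect, false subgroup claims are bounded by 8 × 0.625% = 5%.
   - **Exploratory label.** Subgroup results are reported as estimates with confidence intervals only, and the alpha statement is removed.

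Either rule is a change of wording and needs no extra clusters or data. Under the gate, no confirmatory subgroup claim is possible when the overall test is not significant; under the exploratory label, none is possible at all.

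### The 16 clusters per arm said to be needed for the subgroup analyses is the whole-trial number at a stricter alpha; no subgroup reaches 80% power with it

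*Protocol article*

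**What the plan says.** The Sample Size section of the protocol article lists its assumptions:

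- "Expected average cluster size of 250 eligible women"
- 15% well-managed in the control group, with an "Expected absolute increase of 10% in the proportion of overall well-managed women in the experimental group"
- "Coefficient of variation taking into account the possibility of varying cluster sizes of 1.2"
- a precision assumption "which would lead to a 0.029 intracluster correlation using a beta-binomial model"
- "A power of 80% and a 5% 2-tailed significance level"

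From these it obtains 10 clusters per arm, 20 in total.

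It then considers subgroup analyses by population density, medical density of the department (high or low) and setting (rural or urban). Each is given alpha = 2.5%/8 = 0.3125%, "in order to be able to remain with a 5% 2-tailed significance level for the overall effect". It concludes that "approximately 16 clusters in each arm (32 clusters in total) will be required for the subgroup analyses". The abstract gives 32 clusters as the size of the trial.

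The Randomization section allocates clusters 1:1 by simple randomization, without stratification on these factors.

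**The concern.** Moving from the whole trial to a subgroup changes two things. The test may be held to a stricter alpha, and fewer clusters are available to it. The section accounts for the first only. It does not divide the clusters among subgroups, assume a larger effect within a subgroup, or accept lower power there.

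This matters because the subgroup statement is the only reason given for 32 clusters rather than 20. A reader would take it that the subgroup analyses were sized at the stated 80% power, and could then treat a non-significant result in, say, rural areas as informative when the analysis had little chance of detecting the planned effect.

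A secondary point concerns alpha. The text says the adjustment protects the 5% level for the overall effect, but does not show how eight subgroup tests plus an overall test at 5% achieve this.

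**Working it through.** **Inputs (Sample Size section).** p1 = 0.15, p2 = 0.25, m = 250 women per cluster, ICC = 0.029, factor 1.2, power 80%, alpha 5% two-sided overall and 0.3125% per subgroup analysis. The article does not state its formula, so the first step is to find one that returns its figures.

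**Step 1: the plan's 10 per arm.**
- Women per arm without clustering, two-sided 5%: 250 with pooled variance under the null; 247 unpooled, from (1.960 + 0.842)² x (0.1275 + 0.1875) / 0.10².
- Design effect: 1 + 249 x 0.029 = 8.22. With 1.2 as a plain multiplier: 8.22 x 1.2 = 9.87.
- Clusters per arm: 250 x 9.87 / 250 = 9.9 (pooled) or 247 x 9.87 / 250 = 9.8 (unpooled). Rounded up, this is the stated 10.

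**Step 2: the plan's 16 per arm.** Change alpha only, to one-sided 0.3125% (two-sided 0.625%, critical value 2.734).
- Women per arm: 408 (pooled) or 403 (unpooled).
- Clusters per arm: 408 x 9.87 / 250 = 16.1, or 403 x 9.87 / 250 = 15.9. This is the stated figure of approximately 16.
- As a ratio: (2.734 + 0.842)² / (1.960 + 0.842)² = 1.63, and 9.8 x 1.63 is about 16.

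Both figures are therefore the same whole-trial calculation at two alphas. The 16 assumes that all clusters in an arm enter the one comparison.

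**Step 3: clusters in a subgroup.**
- *Crossed reading.* Three factors at two levels give 2 x 2 x 2 = 8 cells, matching the divisor 8. Then 16/8 = 2 clusters per arm per cell on average. Two levels for population density is inferred, since none are given.
- *One factor at a time.* A level of a two-level factor averages 16/2 = 8 clusters per arm.

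Both are averages. Simple randomization does not assure them.

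**Step 4: power for 15% vs 25% at the alpha that reproduces 16.** The design effect is 9.87. For c clusters per arm, SE = √[(0.1275 + 0.1875) x 9.87 / (250c)]. Normal power is Φ(0.10/SE − 2.734). The t version is noncentral t on 2c − 2 df.

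| Clusters per arm | SE | 0.10/SE | Power, normal | Power, t |
|---|---|---|---|---|
| 2 (crossed cell) | 0.0788 | 1.27 | 7% | 2% (2 df) |
| 8 (level of one factor) | 0.0394 | 2.54 | 42% | 30% (14 df) |
| 16 (whole trial) | 0.0279 | 3.59 | 80% | 74% (30 df) |

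The 80% appears only in the row that uses every cluster.

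**Step 5: size of the gap.** For each of eight cells to have 80% power at the subgroup alpha, each would need 16 clusters per arm: 8 x 16 = 128 per arm, 256 in total, against the planned 32.

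**Step 6: what 32 clusters give the overall effect at two-sided 5%, c = 16.**
- 1.2 as a plain multiplier (design effect 9.87): about 95% (normal), 94% (t).
- 1.2 as a true coefficient of variation in the standard unequal-cluster formula, 1 + [(1.2² + 1) x 250 − 1] x 0.029 = 18.66: about 74% (normal), 71% (t).

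The second design effect does not reproduce the 10 or the 16. It is shown because the text calls 1.2 a coefficient of variation.

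**The case against.** The strongest reply is that the subgroup sentence is conditional, that the article nowhere calls these analyses confirmatory, and that medical density and rural or urban setting are not named as factors in the outcome or analysis sections. The primary comparison also gains, since 32 clusters exceed the 20 calculated for it. All of this stands and limits the seriousness of the point. It does not rescue the sentence, which states a number as what the subgroup analyses require.

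A reader might also infer more than the article supports:

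- **That every subgroup certainly has 2 clusters per arm and almost no power.** This needs the full crossing, which is inferred. If population density had four levels, 4 + 2 + 2 would also make 8 subgroups taken one factor at a time. For a two-level factor, power is then 30% to 42%: inadequate, but not negligible.
- **That the error rate totals 7.5%** (2.5% for the subgroups plus 5% overall). The alpha that reproduces 16 is one-sided, so this sum mixes a one-sided with a two-sided level. The article does not show how 5% is kept, but it does not establish any particular total either.
- **That the correct figure at two-sided 0.3125% is 18 rather than 16.** This depends on the formula. With the 1.2 multiplier it is 17.9 to 18.1; without it, the pooled formula gives 15.1, which rounds up to 16. As the formula is not stated, no error is shown here.

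**Conclusion.** The statement that 32 clusters are required for the subgroup analyses is wrong as written. Sixteen per arm is the number for one comparison using all clusters at a stricter alpha. At the matching alpha, power within a subgroup is about 2% to 7% on the crossed reading and about 30% to 42% for one level of a two-level factor, against the stated 80%.

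These figures assume the section's own effect, cluster size and ICC, with 1.2 as a plain multiplier, the reading under which both 10 and 16 reproduce from one formula. A design effect of 8.22 (no factor for varying cluster size) raises them only to about 9% and 52% (normal), so the conclusion does not hinge on that choice.

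This should be fixed, but it does not undermine the trial. The flaw lies in the reason given for the trial's size, and it does not harm the overall comparison. The unclear account of alpha is secondary.

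**What to change.** 1. Delete the statement that 32 clusters are required for, or give power to, the subgroup analyses.
2. Justify 32 clusters by the overall effect, with restated power at two-sided 5%. Say how 1.2 enters: about 94% to 95% if it is a plain multiplier, about 71% to 74% if it is a true coefficient of variation in the standard unequal-cluster formula. In the second case the stated 80% is not met, so the choice has to be explicit.
3. Label the subgroup analyses exploratory and report them as estimates with confidence intervals, for example from treatment-by-factor interactions. The 2.5%/8 rule is then not needed, and the question of how it keeps the overall level at 5% falls away.

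The change is to wording only and adds no clusters or women. The sponsor gives up any claim that the subgroups are adequately powered, which the design does not support.
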